### Serious adverse events (SAEs)

A serious adverse event is any untoward medical occurrence or effect that at any dose:

- results in death;
- is life threatening (at the time of the event);
- requires hospitalisation or prolongation of existing inpatients’ hospitalisation;
- results in persistent or significant disability or incapacity;
- is a congenital anomaly or birth defect;
- Any other important medical event that may not result in death, be life threatening, or require hospitalization, may be considered a serious adverse experience when, based upon appropriate medical judgement, the event may jeopardize the subject or may require an intervention to prevent one of the outcomes listed above.

Mental Health Care Institutions GGZ Altrecht, GGZ inGeest and GGZ Oost-Brabant already have quality guidelines instated, which include safety protocols (e.g., the Quality Law for Health Institutions– de Kwaliteitswet Zorginstellingen). These will be adhered to in the current study, as treatment will be delivered within the regular treatment procedures. The participating centers will notify the primary investigator ([name]) of possible SAEs within 24 hours.

0

The sponsor will report the SAEs through the web portal *ToetsingOnline* to the accredited METC that approved the protocol, within 15 days after the sponsor has first knowledge of the serious adverse events.

SAEs that result in death or are life threatening should be reported expedited. The expedited reporting will occur not later than 7 days after the responsible investigator has first knowledge of the adverse event. This is for a preliminary report with another 8 days for completion of the report.

*< If certain SAEs do not require immediate reporting, please specify these SAEs as well as the frequency of reporting of these SAEs in line listings.*>

### Suspected unexpected serious adverse reactions (SUSARs)

<This c*hapter is only applicable for studies with an investigational medicinal product>*

Adverse reactions are all untoward and unintended responses to an investigational product related to any dose administered.

Unexpected adverse reactions are SUSARs if the following three conditions are met:

1. the event must be serious (see chapter 9.2.2);
2. there must be a certain degree of probability that the event is a harmful and an undesirable reaction to the medicinal product under investigation, regardless of the administered dose;
3. the adverse reaction must be unexpected, that is to say, the nature and severity of the adverse reaction are not in agreement with the product information as recorded in:

- Summary of Product Characteristics (SPC) for an authorised medicinal product;
- Investigator’s Brochure for an unauthorised medicinal product.

The sponsor will report expedited the following SUSARs through the web portal *ToetsingOnline* to the METC:

- SUSARs that have arisen in the clinical trial that was assessed by the METC;
- SUSARs that have arisen in other clinical trials of the same sponsor and with the same medicinal product, and that could have consequences for the safety of the subjects involved in the clinical trial that was assessed by the METC.

The remaining SUSARs are recorded in an overview list (line-listing) that will be submitted once every half year to the METC. This line-listing provides an overview of all SUSARs from the study medicine, accompanied by a brief report highlighting the main points of concern.

The expedited reporting of SUSARs through the web portal ToetsingOnline is sufficient as notification to the competent authority.

The sponsor will report expedited all SUSARs to the competent authorities in other Member States, according to the requirements of the Member States.

The expedited reporting will occur not later than 15 days after the sponsor has first knowledge of the adverse reactions. For fatal or life threatening cases the term will be maximal 7 days for a preliminary report with another 8 days for completion of the report.

*< For multicentre studies the responsibilities of investigators in participating centres as well as of the coordinating investigator should be clearly defined>*

<*Please describe also the method of breaking the code for SUSAR reporting*.>

## Annual safety report

<This c*hapter is only applicable for studies with an investigational medicinal product>*

< *The annual safety report may be combined with the annual progress report (see chapter 12.4)*.>

In addition to the expedited reporting of SUSARs, the sponsor will submit, once a year throughout the clinical trial, a safety report to the accredited METC, competent authority, and competent authorities of the concerned Member States.

This safety report consists of:

- a list of all suspected (unexpected or expected) serious adverse reactions, along with an aggregated summary table of all reported serious adverse reactions, ordered by organ system, per study;
- a report concerning the safety of the subjects, consisting of a complete safety analysis and an evaluation of the balance between the efficacy and the harmfulness of the medicine under investigation.

## Follow-up of adverse events

All AEs will be followed until they have abated, or until a stable situation has been reached. Depending on the event, follow up may require additional tests or medical procedures as indicated, and/or referral to the general physician or a medical specialist.

SAEs need to be reported till end of study within the Netherlands, as defined in the protocol

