# Measurements are taken at four fixed 6-10-week intervals (depending on the type of anxiety treatment); at baseline (T0), week 6-10, week 12-20 and at weeks 64-72 (52 weeks follow-up) (T1 – T3). The recruitment of participants aims to start April 2015 (first patient in; after Medical Ethics (METC) consent) and the inclusion ends at December 2016, and the follow up at December 2017. For detailed information on the sample size and power calculation, see the study protocol.

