### TiC-P is the most widely used health service receipt interview for economic evaluations in the Netherlands. The TiC-P consists of 46 questions, divided over two parts. Part 1 entails the health care uptake at relevant health care providers in the past 4 weeks, such as medication intake, and the number of contacts within the mental health care setting, with the GP and with other medical specialists. To determine the costs associated with these contacts, the care consumption is multiplied by the cost price described in the before mentioned guideline. Part 2 of the TiC-P entails loss of productivity in the past 4 weeks. This is measured by enquiring about the number of days absent from work and the number of days with reduced efficiency due to feeling ill. The costs of productivity losses will be based on the gender and age specific friction costs, as outlined in the Dutch guideline for costing (Hakkaart van Roijen L, 2010).

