**Table 1: Overview of measurements for anxiety.**

| **Questionnaire** | **Baseline**  **Start treatment**  **(T0)** | **Week 6-10**  **Mid-treatment**  **(T1)** | **Week 12-20**  **End treatment**  **(T2)** | **Week 64-72**  **Follow-uptreatment**  **(T3)** |
| --- | --- | --- | --- | --- |
| **Primary outcomes** |  |  |  |  |
| BAI (anxiety severity) | x | x | x | x |
| SCID-I full diagnostic interview | x |  |  | x |
| EQ-5D (general well-being) | x | x | x | x |
| SF-36 (health-related quality of life) | x | x | x | x |
| TiC-P (health-care utilization) | x | x | x | x |
|  |  |  |  |  |
| **Secondary outcomes** |  |  |  |  |
| PDDS (panic disorder, if applicable) | x | x | x | x |
| LSAS (social anxiety, if applicable) | x | x | x | x |
| PSWQ (Generalized Anxiety Disorder, if applicable) | x | x | x | x |
| BDI (depression) | x | x | x | x |
| WSAS (work and social adjustment) | x | x | x | x |
| BSI (general psychopathology) | x | x | x | x |
| CSQ (satisfaction)  Mastery Scale (locus of control)  WAI (therapeutic alliance)  SUS (system usability, bCBT only) | x | x  x | x  x | x  x |

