## Study procedures

Patients will be recruited within outpatient Anxiety Disorder departments of the participating Mental Health Care site(s) of GGZingeest, GGZ Altrecht and GGZ Oost-Brabant in the Netherlands. During their intake interview, all new patients indicate whether they are willing to participate in a study. All patients with a primary diagnosis of a severe anxiety disorder (panic disorder with or without agoraphobia, social phobia, and generalized anxiety disorder) who are willing to participate will be approached by the researchers by telephone and asked to participate in the study. Participants then receive a letter containing information on the study and the informed consent form (including a return envelope).

After a week, the researchers will contact the patient again. When the patient is willing to participate, a trained researcher then screens the patients with respect to the inclusion and exclusion criteria based on the SCID-I diagnosis and the patient’s demographic characteristics, such as age.

Patients who are not eligible to participate will be notified and remitted to regular treatment trajectories within the participating specialized mental health care center(s).

If patients are eligible to participate, written informed consent will be obtained. Subsequently, patients receive an email containing an invitation to fill in the online questionnaires. When the baseline measures are completed, patients are randomized to either bCBT or CBT-TAU. Treatment duration is 12-20 weeks in the bCBT group and 12-20 weeks in the CBT-TAU group. When necessary, additional treatments are allowed for all patients at any point of time during the study.

After 6-10, 12-20 and after 64-72 weeks (52 weeks follow-up), the patient is asked to complete a number of measures (see Table 1), which consist of a diagnostic interview (SCID-I and a set of online questionnaires).

At week 64-72 (52 weeks follow-up) the full SCID-I interview is administered to assess whether the anxiety disorder is present and to determine co-morbid disorders. The SCID-I can be administered via the telephone and face-to-face at a the mental health care location, depending on patient preference. A full SCID-I interview takes 60 minutes at most. Administering sections on anxiety disorders takes about 10 minutes.

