The self-report questionnaires are administered online. Patients receive an email with a personal link to their questionnaires and have one week to fill them in. The questionnaires take 30 to 45 minutes to complete.
If the measurements that are administered in the study (during and after treatment) indicate signs of relapse or suicidal ideation, the investigator will contact the therapist immediately.

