## End of study report

<*The following text is applicable for studies without an investigational medicinal product*.>

The investigator will notify the accredited METC of the end of the study within a period of 8 weeks. The end of the study is defined as the last patient’s last visit.

In case the study is ended prematurely, the investigator will notify the accredited METC within 15 days, including the reasons for the premature termination.

 Within one year after the end of the study, the investigator/sponsor will submit a final study report with the results of the study, including any publications/abstracts of the study, to the accredited METC.

<*The following text is applicable for studies with an investigational medicinal product.*>

The sponsor will notify the accredited METC and the competent authority of the end of the study within a period of 90 days. The end of the study is defined as the last patient’s last visit.

In case the study is ended prematurely, the sponsor will notify the accredited METC and the competent authority within 15 days, including the reasons for the premature termination.

 Within one year after the end of the study, the investigator/sponsor will submit a final study report with the results of the study, including any publications/abstracts of the study, to the accredited METC and the Competent Authority.

<*In case the final study report will not be available within one year, another term should be defined including the reasons.*>

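### SAEs are reportable until end of study, but for the 52 weeks before T3 their collection is passive only, and the post-treatment alert names only the therapist

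*Protocol*

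**What the plan says.** **Reporting period.** Protocol section 9.4: "SAEs need to be reported till end of study within the Netherlands, as defined in the protocol". Section 12.5: "The end of the study is defined as the last patient’s last visit". That definition is the same in both template variants left in section 12.5.

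**Schedule.** Section 8.3: "Treatment duration is 12-20 weeks in the bCBT group and 12-20 weeks in the CBT-TAU group". Section 3 places the measurements "at baseline (T0), week 6-10, week 12-20 and at weeks 64-72 (52 weeks follow-up) (T1 – T3"). Table 1 has no column between T2 and T3.

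**Sources of safety information.** Section 9.2.1 records adverse events that the subject volunteers or that the investigator or staff observe. Section 9.2.2 has the centres notify the primary investigator of possible SAEs within 24 hours, and the sponsor then reports to the ethics committee. On the centres' own quality guidelines and safety protocols it says: "These will be adhered to in the current study, as treatment will be delivered within the regular treatment procedures".

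**What is asked at T3.** Table 1 lists the "SCID-I full diagnostic interview" at baseline and T3. Section 8.3 gives its purpose at T3 as establishing whether the anxiety disorder is present and which comorbid disorders exist. The TiC-P is also given at T3; of it, section 8.1 says: "Part 1 entails the health care uptake at relevant health care providers in the past 4 weeks".

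**Alert.** Under section 8.3, if measurements taken while treatment runs or after it has finished point to relapse or suicidal ideation, "the investigator will contact the therapist immediately". Section 11.2 has a differently worded recipient for an acute suicide threat found at screening: there the principal investigator informs whichever professional is responsible for the patient's treatment.

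**The concern.** The protocol fixes a reporting period that runs well past treatment, while its means of learning about events fit the treatment phase best. During therapy a clinician sees the patient regularly and can notify an admission or a suicide attempt. After T2 the study arranges no contact for a year, and when it does make contact it does not ask what happened in between. An event in that year is recorded only if the patient volunteers it or the centre happens to learn of it and passes it on. The SAE information sent to the ethics committee each year (section 12.4) would then be least complete for the longest part of participation.

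The alert raises a second issue. It is meant to work on T3 data, but its one recipient is defined by a treatment that, on the protocol's own schedule, is over by then. Followed literally, a signal of suicidal ideation could go to someone who is no longer treating the patient.

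Nothing elsewhere in the protocol clearly fills either gap. Section 9.5 on a safety board is largely unfilled template text, and section 12.2 foresees no monitoring of study procedures beyond data-management support and a possible random audit.

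**Working it through.** **1. Length of the interval.** Inputs: end of treatment and T2 at week 12-20, T3 at week 64-72 (sections 3 and 8.3). Pairing the short and the long treatment courses:

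- 64 − 12 = 52 weeks
- 72 − 20 = 52 weeks

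This reproduces the protocol's stated 52-week follow-up. Crossing the ends of the ranges would give 64 − 20 = 44 and 72 − 12 = 60 weeks, but the stated 52 weeks shows that the paired reading is intended.

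**2. Share of each patient's time in the study.**

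- 52/72 = 0.722, or 72%
- 52/64 = 0.8125, or 81%

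**3. Is the interval inside the SAE period?** Yes. Reporting runs to end of study, and end of study is the last patient's last visit, so every patient's T2-T3 interval and T3 itself are covered.

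**4. What collects SAEs in that interval?**

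| Source | Section | Active between T2 and T3? | Does anyone ask the patient? |
| --- | --- | --- | --- |
| Spontaneous report | 9.2.1 | Yes, no cut-off stated | No |
| Observation by investigator or staff | 9.2.1 | Only if there is contact; none is scheduled | No |
| Centre notification within 24 hours | 9.2.2 | Yes, no time limit stated | No; depends on the centre learning of the event |

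**5. Does T3 recover the interval?** Not as described. The diagnostic interview serves diagnosis and comorbidity. The TiC-P is a cost instrument with a look-back of 4 weeks (section 8.1) or three months (section 10.1), so it does not span the 52 weeks on either description. No other measure listed for T3 is described as covering events since T2.

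**6. The alert.** Its source exists at T3, namely the T3 measurements. Its scope expressly includes measurements after treatment. Its recipient is the therapist, whose study treatment ended about 52 weeks earlier by step 1. Section 11.2 uses different recipient wording, but only for the screening stage.

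No sample size, power or error-rate calculation depends on this point.

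**The case against.** The strongest reply is that the plan does have a safety channel after treatment, and that passive collection is a deliberate and common choice in a comparison of two ways of delivering CBT within routine care. Much of this stands. A reader might infer four stronger conclusions, and the protocol supports none of them.

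- **That the SAE channel or the alert stops working after T2.** The channel has a recipient throughout (primary investigator, then sponsor, then ethics committee). Spontaneous reports and the 24-hour centre duty have no end date. The remark about treatment within regular procedures explains why the centres' own guidelines apply; it does not limit the notification duty. The alert has a source at T3, and only its recipient is in doubt.
- **That patients are discharged at T2.** The protocol never says so. Section 8.3 allows additional treatment at any time, and section 5 places pharmacotherapy with a psychiatrist independently of the study. Some patients will still have a clinician, perhaps the same therapist. What is missing is a rule for those who do not.
- **That 92% or 75% of the follow-up year is unseen.** Those figures are (52 − 4)/52 = 0.92 and (52 − 13)/52 = 0.75. They measure the recall gap of a cost questionnaire that is never named as an SAE source, and they give no credit to the passive sources.
- **That a safety result would be biased.** The statements that blended care adds no risk (Summary and section 11) are advance assessments for the ethics committee. They are not conclusions drawn from trial SAEs, and the protocol plans no comparative SAE analysis.

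The sentence in section 9.4 is also not wrong in itself. The weakness lies in sections 8.3 and 9.2, which do not fully support it. The reply does not answer two points: nobody asks about the year when the patient is next contacted, and the alert covers post-treatment data without saying whom to contact when therapy is over.

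**Conclusion.** The point holds in this form. SAEs are reportable for the whole study, but for the 52 weeks from T2 to T3, 72% to 81% of each patient's time in the study, ascertainment is passive only, and T3 does not make up for it. Events in that year could go unrecorded; how many cannot be estimated from the document. The alert for relapse or suicidal ideation covers post-treatment measurements but has no stated recipient for a patient who has left therapy.

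This rests on the paired reading of the visit weeks, which the stated 52-week follow-up confirms, and on the T3 instruments being used as the protocol describes them. It is a safety-procedure weakness with no effect on the primary economic analysis. It deserves correction because the alert concerns suicidality and a better method is available at little cost.

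**What to change.** 1. **Sections 8.3 and 9.4.** Add to the existing T3 interview or online form a fixed question covering the whole period since T2, on each SAE category in section 9.2.2 that a patient can report: hospital admission, life-threatening event, lasting disability, other important medical event. State in section 9.4 that this is how the T2-T3 interval is ascertained, alongside the passive sources.
2. **Section 8.3.** Reconcile the alert sentence with the treatment schedule in the same section and with the recipient wording in section 11.2, so that a signal arising after treatment has a stated recipient for patients no longer in therapy. Who that is, and what they do on receiving it, is for the sponsor to define.

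Cost: a few minutes at a contact that already takes place, slightly more SAE reports to process, and a short text change. Patients who are not reached at T3 would still depend on passive reporting.

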## [Data Safety Monitoring Board (DSMB) / Safety Committee]

<*In case a DSMB is established to perform ongoing safety surveillance and to perform interim analyses on the safety data, this committee should be an independent committee. The composition of the DSMB should be described and it should be clear that each member has no conflict of interest with the sponsor of the study*.

*The task and responsibility of the DSMB should be described (see chapter 10.4 for interim analyses either for safety or for futility or positive efficacy)* >

<*Criteria on which the DSMB may decide to terminate the trial prematurely should be clearly defined before the trial has started.*>

The advice(s) of the DSMB will only be sent to the sponsor of the study. Should the sponsor decide not to fully implement the advice of the DSMB, the sponsor will send the advice to the reviewing METC, including a note to substantiate why (part of) the advice of the DSMB will not be followed.

*< In case a DSMB is not needed, but some safety review is deemed appropriate, information on this safety committee should be given here. Information should be provided on the composition of the committee and (in)dependence of the members, the reason to establish this committee, type of data that will be reviewed and moment of review, possible measures to be taken>*

# STATISTICAL ANALYSIS

## Primary analyses

A cost-effectiveness analysis (CEA) and cost-utility analysis (CUA) will be conducted from the societal perspective. In addition, a budget impact analysis (BIA) will be based on a health-economic modeling study in agreement to Mauskopf’s recommendations (2007), i.e. from the perspective of the public purse, the health care insurer and the service-provider.

**CEA/CUA**

Costs will be assessed at pre-, mid-, post-treatment and at one-year follow up. As the TIC-P cost date covers a period of three months, all costs will be extrapolated to a 12 months period assuming a stability of costs during the time frame. T-tests will test the change for each cost domain. As cost data will not be normally distributed, p-values will be estimated using a multilevel model (with repeated measurements to control for dependency between the measurements) after which a bootstrap analysis on the parameters is performed (10,000 replications, to generate a reliable cost estimate [23]. An incremental cost-effectiveness ratio (costs per case response or remission) and will be calculated (ICER =(mean costs blended eHealth treatment-mean costs TAU)/(mean bCBT -mean CBT-TAU). The mean costs, including all medical and non medical costs, of the patients in the blended eHealth condition will be subtracted from the mean costs of the patients in the TAU condition. This difference will be then be divided with the subtracted effects (case of response or remission on the BAI). This procedure will be bootstrapped 10,000 times, generating an estimation of the blended eHealth treatment groups’ incremental costs in relation to their incremental health benefit. Additionally an incremental cost-utility ratio (costs per QALY) will be calculated; this procedure is identical to the cost-effectiveness ratio with the exception that instead of a case of response or remission, an additional quality adjusted life year is calculated (QALY). Finally, to test the robustness of the results, we will conduct a sensitivity analyses, to investigate how sensitive the ICERs will be to changes of cost estimates (for example difference in costs per iCBT contact, type of psychologists and number of sessions). For decision-making purposes, the ICER acceptability curve will be plotted for various willingness-to-pay (WTP) ceilings, which helps making judgments about whether the blended intervention offers good value for money, relative to treatment as usual. One-way sensitivity analyses directed at uncertainty in the main cost drivers will be performed to gauge the robustness of our findings across a range of likely values of those parameters.

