## Sample size calculation

In economic evaluations we are calculating the power to estimate the joint distribution of costs and treatment effects. Subsequently, we need more information for estimating power compared to clinical trials, namely expected costs of treatments, expected covariance of treatment effects/costs, and the maximum willingness to pay for the treatment effect. To incorporate this information, the formula of Glick et al. (2011) can be used. A goal of sample size and power calculation for cost-effectiveness analysis is to identify the likelihood that an experiment will allow us to be confident that a therapy is acceptable or not when we adopt a particular willingness to pay.

For this study a sample size of 156 is based on a formula to estimate the power of a cost-effectiveness analyses. (Glick, 2011)

$$n=\frac{{2(z_{\alpha}+z_{\beta)}}^{2}\left( {sd}^{2}+\left( W^{2}{sd}^{2} \right)-\left( 2W\rho{sd}_{c}{sd}_{q} \right) \right)}{\left( WE-C \right)^{2}}$$

$$n=sample size/group$$

$$z_{\alpha}=z statistics for alpha$$

$$z_{\beta}=z statistics for Beta$$

$${sd}_{c}=Expected standard deviation costs$$

$${sd}_{e}=Expected standard deviation effects$$

$$W=Willingness to pay$$

$$C=Expected differences in costs$$

$$E=Expected differences in effects$$

$$\rho=correlation between differences in costs and effects$$

($z_{\alpha}=1,96$, $z_{\beta}=0,84$,${sd}_{c}=800$, ${sd}_{e}=0,02$, $W=80,000, C=832,E=0,02 \rho=0,1)$

Following the formula, we may expect that the point estimate for the cost-effectiveness ratio will be around 40,000 per quality- adjusted life year (QALY), using only a small increase in quality of life and lower costs for blended eHealth, we want to design an experiment that will provide an 80% chance (i.e., power) to be 95% confident that the therapy is good value when we are willing to pay at most 80,000 per QALY. In the Netherlands, a costs-effectiveness ratio between 20.000 and 80.000 Euro per QALY is assumed acceptable.

Glick, H.A. (2011). Sample size and power for cost-effectiveness analysis (part 1). Pharmacoeconomics, 29 (3), 189-198.

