**Cost outcomes**
Cost estimates include 1) the costs of offering the treatments and 2) Patients’ out-of-pocket costs (non-medical), such as the costs of travelling to the health services and the patients’ time costs of travelling, waiting and receiving treatment, which are determined with the standard cost prices as listed in the pertinent Dutch guideline for economic evaluation (Tan et al., 2012). Furthermore, 3) Costs stemming from health care uptake, including costs of medication, and 4) Costs stemming from productivity losses due to absenteeism and lesser efficiency while at work (presenteeism) are assessed with *The Trimbos/iMTA questionnaire for Costs associated with Psychiatric Illness* (TiC-P; Hakkaart – van Roijen et al., 2002.

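### The protocol gives the TiC-P two recall periods, 4 weeks and three months; if the 4-week form is scaled by the three-month rule, TiC-P-derived costs are understated 3.25-fold

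*Protocol*

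**What the plan says.** Protocol Section 8.1.2 (cost outcomes) lists four cost categories. Treatment costs and patients' out-of-pocket and time costs come first. Health-care uptake with medication and productivity losses come next, and these two are collected with the TiC-P.

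The TiC-P paragraph gives the recall period separately for each part. For health care: "Part 1 entails the health care uptake at relevant health care providers in the past 4 weeks". For work: "Part 2 of the TiC-P entails loss of productivity in the past 4 weeks".

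Section 10.1 (CEA/CUA) sets the costing rule for the primary analysis. On timing: "Costs will be assessed at pre-, mid-, post-treatment and at one-year follow up". On annualisation: "As the TIC-P cost date covers a period of three months, all costs will be extrapolated to a 12 months period", and this is done "assuming a stability of costs during the time frame". The rule gives no numerical multiplier.

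**The concern.** Both sections describe the same questionnaire, and a given form has one recall window for each question. Section 10.1 does not mention three months in passing: it is the reason given for the extrapolation. An analyst who follows that rule on the form described in Section 8.1.2 would scale 4 weeks of use as if it were a quarter of a year.

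This matters because the health-economic comparison is the main goal of the study (Section 2), and the ratio's numerator takes in all medical and non-medical costs (Section 10.1). QALYs are built from utilities weighted by time (Section 8.1.1) and do not carry this multiplier, so an error in it does not cancel in the cost per QALY. The same holds for cost per response or remission.

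The planned checks would not expose the problem. The examples given for sensitivity analysis are the cost per online contact, the type of psychologist and the number of sessions. Bootstrapping would repeat a scaling error in every replicate.

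**Working it through.** **The plan's own figure.** There is none to reproduce, because the protocol never states the multiplier. It has to be inferred from the recall period.

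**Inputs.** Three months extrapolated to 12 months (Section 10.1, CEA/CUA); 4 weeks for both TiC-P parts (Section 8.1.2).

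**Multiplier = length of year / recall period.**

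- Section 10.1: 12 / 3 = 4.
- Section 8.1.2: 52 / 4 = 13.
- Ratio: 13 / 4 = 3.25. Costs multiplied by 4 would be 4/13 = 30.8% of the annual figure.

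**Calendar convention.** By day count, 365.25 / 28 = 13.04, and 13.04 / 4 = 3.26. Taking 4 weeks as one month, 12 / 4 = 3.0. The range is 3.0 to 3.26.

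**If the three-month statement is right.** The correct multiplier is 4 and the factor is 4 / 4 = 1. Annualised costs are then not affected, and only the questionnaire description is wrong.

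**Effect on total annual cost.** Let s be the TiC-P share of true annual cost, and assume that the remaining components are counted correctly. The understatement factor is 1 / (s × 4/13 + 1 − s). The protocol gives no value for s, so these shares are assumptions:

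| Assumed s | s × 4/13 + 1 − s | Factor |
|---|---|---|
| 25% | 0.827 | 1.21 |
| 50% | 0.654 | 1.53 |
| 75% | 0.481 | 2.08 |
| 100% | 0.308 | 3.25 |

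**Effect on incremental cost.** The factor applies to both arms alike, so a TiC-P cost difference between arms shrinks 3.25-fold relative to any difference in components that are not scaled. If the two differences have opposite signs, the net difference could change sign as well as size.

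**Fit with the visit schedule.** T0 to T1 and T1 to T2 are each 6 to 10 weeks apart (Sections 3 and 8.3). A three-month window at T1 would reach back before baseline, and at T2 it would overlap the T1 window. A 4-week window would leave gaps instead. Neither window tiles the schedule, so the schedule does not show which statement is right, and the weights differ in the two cases.

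**The case against.** The strongest case on the other side is that the error is conditional. It needs two things: a fielded form with 4-week recall, and an analyst who multiplies by 4. If the three-month statement describes the form in use, no cost is wrong. This stands, and the point is worded accordingly.

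A benign reading is also possible: three post-baseline recalls of 4 weeks add up to 12 weeks, roughly three months. The multiplier would then be 52 / 12 = 4.33, and using 4 would understate by only 1.08. The protocol mentions no such pooling and counts four cost assessments, so this is conjecture. It is a further reason to state the rule.

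Four stronger inferences are tempting, and the document does not support them:

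- **That total costs are wrong by 3.25.** The factor applies to TiC-P-derived costs only.
- **That the cost per QALY falls from about 41,600 to 12,800.** Section 4.4 expects a cost difference of 832 and an effect of 0.02, so 832 / 0.02 = 41,600. The lower figure treats all of the 832 as TiC-P cost (832 / 3.25 = 256; 256 / 0.02 = 12,800), which Section 4.4 does not say. If a share of 25%, 50%, 75% or 100% of the cost difference came from the TiC-P and the rest were unscaled, the ratio would be 41,600 × (1 − share × 9/13) = 34,400, 27,200, 20,000 or 12,800. All of these lie below the design threshold of 80,000, so in this example the decision at that threshold is unchanged.
- **That treatment-delivery costs keep their true scale.** Section 10.1 says that all costs are extrapolated and exempts none. Section 8.1.2 also has the TiC-P count contacts within mental health care, so how trial sessions are costed is not clear.
- **That the budget impact analysis is distorted.** Section 10.1 (BIA) describes a Markov cohort model, with health-authority tariffs for the public-purse and insurer perspectives. It does not say that annualised TiC-P costs enter it.

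This is also not a detail left to a statistical analysis plan. The recall period is a property of the form that patients complete, and the protocol has stated it in two incompatible ways.

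**Conclusion.** The contradiction is certain; its numerical consequence is conditional. Sections 8.1.2 and 10.1 give different recall periods for the instrument that supplies two of the four cost categories in the primary analysis, and nothing in the protocol settles which applies.

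If the form asks about 4 weeks and the three-month rule is used, TiC-P-derived health-care and productivity costs are understated 3.25-fold. This rests on an implied, unstated multiplier of 4. If the form asks about three months, the size of the error is nil and Section 8.1.2 needs correcting. The shift in total cost, incremental cost and the ratios cannot be fixed from the document, because it depends on the TiC-P share and on which components are extrapolated. The two sections must be reconciled before any cost is annualised.

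**What to change.** 1. Check the recall wording of the TiC-P as fielded in the online questionnaire, for both parts.
2. State that one period in Sections 8.1.2 and 10.1.
3. State the matching annualisation multiplier in Section 10.1 (13 for a 4-week form, 4 for a three-month form), or the interval weights if the four assessments are to be combined over the 6-to-10-week intervals and the 52-week follow-up.
4. Replace the instruction to extrapolate all costs with a list of the components to which the multiplier applies. Say how the costs of the trial treatment are obtained, and whether trial sessions reported in the TiC-P are excluded from the extrapolated costs.

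The cost is a protocol edit and a check of the online form. It needs no extra patients or visits.
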